### Strategies to improve adherence to interventions {11c}

Included patients will join the SYNCOMOT in-patient rehabilitation program in each participating center. The GR rehabilitation protocols will be gradual and personalized, in order to motivate the participants. Trained therapists will ensure that the patients comply with the GR protocol in each session. The level(s) of difficulty (the motor burden and/or the cognitive burden) during the two GR programs will be self-assessed by the patient on VASs at the end of each session and recorded by the therapist. Depending on the patient's progression through the GR protocol, up to 12 intensity levels can be performed. If a patient fails an exercise or session, she/he will repeat the last successfully completed exercise or session. If an exercise is not possible, an alternative exercise will be provided in the protocol and thus will ensure that the patient performs 30 min of GR. If the GR protocol is suspended because of an acute health problem, the 30-min sessions will be rescheduled so that all twelve 30-min training sessions are completed within 31 days.

### Relevant concomitant care permitted or prohibited during the trial {11d}

All types of care will be permitted during the study, other than non-scheduled DT training.

### Provisions for post-trial care {30}

Not applicable.

### Outcomes {12}

#### Clinical assessments at baseline (Table 3)

The study population's characteristics recorded at baseline (M0) will include demographic variables (age, sex, and handedness), comorbidities (neuro-orthopedic and bladder disorders), the stroke date, the type of stroke (site, side, and ischemic or hemorrhagic), the stroke severity (National Institutes of Health Stroke Scale (NIHSS) score) [47], neurological impairment (the motor part of the Fugl-Meyer Assessment of the lower extremity [54], the French adaptation of the Harmonization Standards Neuropsychological Battery [50, 55, 56] (Table 4), personal autonomy (the functional independence measure (FIM) [51]), disability (a structured interview with a modified Rankin scale score (mRS-SI) (Table 5) [52]); and QoL on a VAS (QoL-VAS). Qualitative and quantitative gait variables will be assessed with a clinical classification of gait disorders (Supplementary material 1), the single-task 10-m walking test (ST 10MWT) [61], and the FIM's “walking” item [51]. Balance will be assessed in the timed up-and-go (TUG) test. In order to assess CMI, four cognitive-motor DTs will be performed during the DT 10MWT and the DT TUG test: a verbal Trail Making Test (executive function) [59], a symbolic praxis test [60], a literal fluency test [50], and a verbal serial number recall task (short-term memory [62]). The data from the cognitive-motor DTs will be recorded every 15 s, so that participants can be compared regardless of their gait speed [63].

**Table 3 Tab3:** Schedule for the assessment of primary and secondary outcomes

	Recruitment	Inclusion M0	Follow-up visit at M1	Follow-up visit at M2	Follow-up visit at M6
**Investigator**					
Patient information	✓				
Informed consent		✓			
Demographic data^a^		✓			
Randomization		✓			
Gait classification		✓			
Stroke^b^		✓			
NIHSS		✓	✓	✓	✓
Fugl-Meyer (lower limb)^c^		✓	✓	✓	✓
FIM		✓	✓	✓	✓
mRS-SI		✓	✓	✓	✓
QoL-VAS		✓	✓	✓	✓
AEs and SAEs			✓	✓	✓
**Therapists**					
ST 10 MWT		✓	✓	✓	✓
DT 10 MWT		✓	✓	✓	✓
ST TUG		✓	✓	✓	✓
DT TUG		✓	✓	✓	✓
**Neuropsychologist**					
Neuropsychological battery^d^		✓	✓	✓	✓
**Radiologist**					
MRI	✓ 280 patients in 12 centers (4 and 6 months after stroke)				
fMRI and fMRS	✓ 20 patients at the Amiens center (4 and 6 months after stroke)				

^a^Age, sex, handedness, and comorbidities (bladder disorders and neuro-orthopedic complications)

^b^Stroke site, side, and type (ischemic or hemorrhagic)

^c^The motor part of the Fugl-Meyer Assessment of the lower extremity [47]

^d^Assessment of neuropsychological cognitive abilities, using the French adaptation [29] of the Harmonization Standards protocol [48]; assessment of behavioral dysexecutive disorders, using the previously validated Behavioral Dysexecutive Syndrome Inventory) [49]

*NIHSS* National Institutes of Health Stroke Scale, *FIM* the Functional Independence Measure [50], *mRS-SI* a structured interview with a modified Rankin score [51], *QoL-VAS* visual analog scale for quality of life, *AE* adverse event, *SAE* serious adverse event, *ST 10MWT* single-task 10-meter walk test [52, 53], *DT 10MWT* dual-task 10-m walk test, with four cognitive tasks during gait, the verbal Trail-Making Test (executive function), a symbol praxis task, a literal fluency task, and a verbal serial recall task (short-term memory), *ST TUG* single-task timed up-and-go test, *DT TUG* dual-task timed up-and-go test, with four cognitive tasks during gait, the verbal Trail-Making Test (executive function), a symbol praxis task, a literal fluency task, and a verbal serial recall task (short-term memory), *MRI* magnetic resonance imagery, *fMRI* functional MRI, *fMRS* functional magnetic resonance spectroscopy

**Table 4 Tab4:** The validated French adaptation of the Harmonization Standards Neuropsychological Battery for stroke, for describing cognitive functions at the M0, M1, M2, and M6 visits [48, 55]

SYNCOMOT will assess appropriate cognitive abilities (using the French adaptation [29] of the Harmonization Standards Neuropsychological Battery [48]) and behavioral dysexecutive disorders (using the previously validated Behavioral Dysexecutive Syndrome Inventory (BDSI)) [49]	
- Detecting global cognitive impairments:	
• Mini-Mental State Examination [57]	
- *Detection of the main cognitive disorders:*	
• Phasic: center using scale except Battery for the Evaluation of Lexical Disorders [58]	
• Praxis: Florence Mayeux’s symbolic praxis test [59]	
• Memory: short-term memory with an immediate verbal serial number recall (Baddeley task) and long-term verbal and visual memory	
• Spatial neglect: Albert’s test	
- Description of executive functions:	
• Flexibility of attention: Trail-Making Test parts A and B [48]	
• Dual task performance: Baddeley task [60]	
• Inhibition: Stroop tasks [48]	
• Verbal fluency: literal fluency (“P” at M0, “V” at M1, “R” at M2 and “B” at M6)	
• Processing speed index (PSI): third edition of the Wechsler adult intelligence scale (WAIS-III)	
• Dysexecutive behavior syndrome (BDSI) [49]	
- Detection of mood disorders:	
• Depression assessment on the Montgomery-Asberg Depression Rating Scale (MADRS) [90]	
• Anxiety assessment on the Goldberg scale [91]

**Table 5 Tab5:** Structured interview of modified Rankin Score (mRS-SI): an English translation of the French-validated mRS-SI

**mRS-SI 5**	**Bedridden: ‘Is the person bedridden?’**	
	- The patient is unable to walk even with another person’s assistance.	**Yes □ No □**
	- If placed in a wheelchair, unable to self-propel effectively.	
	- May frequently be incontinent.	
	- Requires nearly constant care (provided by either a trained or untrained caregiver): someone needs to be available nearly at all times.	
**mRS-SI 4**	**Assistance to walk: ‘Is another person’s assistance essential for walking?’**	
	- Requiring another person’s assistance means needing another person to be always present when walking, including indoors around house or ward, to provide physical help, verbal instruction, or supervision.	**Yes □ No □**
	- Patients who use physical aids to walk (stick, walker) but do not require another person’s help, are NOT rated as requiring assistance to walk.	
	- For patients who use wheelchairs, patient needs another person’s assistance to transfer into and out of chair, but can self-propel effectively without assistance.	
**mRS-SI 3**	**Assistance to look after own affairs**^**1**^**:** “Could the patient live alone for 1 week if he/she absolutely had to?”	
3.1	- Is assistance essential for preparing a simple meal?	**Yes □ No □**
3.2	- Is assistance essential for basic household chores?	**Yes □ No □**
3.3	- Is assistance essential for looking after household expenses and to manage day-today purchases?	**Yes □ No □**
3.4	- Is assistance essential for local travel and transportation?	**Yes □ No □**
3.5	- Is assistance essential for taking medication in correct dosages at correct time (includes preparation in advance, recall and supervision)?	**Yes □ No □**
3.6	- Telephone use: Is assistance essential for look up and dial numbers?	**Yes □ No □**
**mRS-SI 2**	**Limitations in participation in usual duties and activities:** “has there been a change in the person’s ability to work or look after others or participate to leisure activities as compared with prestroke status? This supposes that it is due to the new stroke itself.”	
2.1	- Has the stroke substantially reduced the person’s ability to work or, for a student, to study? (Change from full-time to part-time, change in level of responsibility, or unable to work at all).	**Yes □ No □**
2.2	- Has the new stroke substantially reduced the person’s ability to look after family at home?	**Yes □ No □**
2.3	- Has the new stroke reduced the person’s regular free-time activities^2^?	**Yes □ No □**
2.4	- Is this reduction in activity related to a physical/medical problem other than the stroke? If yes which one? Details:	**Yes □ No □**
**mRS-SI 1**	**Persisting symptoms as a result of the stroke:** “Does the patient have any symptoms resulting from the new stroke?” “Does the person have:”	
	- Difficulty reading or writing?	**Yes □ No □**
	- Difficulty speaking or finding the right word?	**Yes □ No □**
	- Problems with balance or coordination?	**Yes □ No □**
	- Visual problems as a result of the stroke?	**Yes □ No □**
	- Numbness (face, arms, legs, hands, feet)?	**Yes □ No □**
	- Weakness or loss of movement (face, arms, legs, hands, feet)?	**Yes □ No □**
	- Difficulty with swallowing	**Yes □ No □**
	- Sleeping difficulty?	**Yes □ No □**
	- Headaches as a result of stroke?	**Yes □ No □**
	- Otherwise unexplained reduction of activities, anxiety, depressive mood, or sadness repetitive concerns (especially about his/her health or situation)?	**Yes □ No □**
	- Loss of consciousness?	**Yes □ No □**
	- Other symptoms? Details:	**Yes □ No □**

1. Assistance includes physical help, verbal instructions, or supervision by others

2. Social and leisure activities include activities outside the home or at home; Activities outside the home: going to the coffee shop, bar, restaurant, club, church, cinema, visiting friends, going for walks; Activities at home: involving “active” participation including knitting, sewing, painting, games, reading books, home improvements

**Procedure**: Examiners had to read each proposal to the patient and caregiver and when impairment was detected, the corresponding Rankin grade had to be selected. The examiner might also gather data from other sources, such as records, nurse notes, and medical files. The examiner was instructed to rate what the patient actually did. The only exceptions concerned situations where the patient could clearly perform the activity in a fully independent manner but it was not performed for contextual reasons: patients able to work but not returning to work because the stroke occurred just before retirement (early retirement); patient able to perform basic activities but the carer prefers to do them because of time pressure; patient not confronted with specific activities (complex financial activities, transportation, meal preparation) since hospital discharge

#### The primary outcome measure

Gait speed is the “gold standard” measure of gait performance [64]. At the subacute stage of stroke, speed was recently estimated to be 0.34 m.s^−1^, i.e., a 70% decrease [53]. The ST 10MWT will be used to assess gait performance in the DT GR and ST GR groups at post-stroke M6. This test is a key indicator of functional gait performance, the risk of falls, and decline after stroke [40, 41]; it constitutes the gold standard for the provision of quantitative data on gait performance. Performance in the 10MWT is known to be related to community ambulation ability and QoL [10, 53, 63–66].

#### Secondary outcome measures

The secondary outcomes measures will be (i) motor performance (lower limb motricity, gait, and balance), (ii) cognitive performance, (iii) autonomy, (iv) disability, and (v) QoL in the short, medium, and long term after stroke, as a function of gait characteristics and post-stroke plasticity. In order to evaluate short-, medium- and long-term effects, these outcomes will be assessed at M1, M2, and M6, respectively. The classification of the various gait characteristics at baseline will describe the epidemiology of gait disorder phenotypes at the sub-acute stroke stage.

### Participant timeline {13}

The participant timeline is shown in Fig. 1.

### *Sample size {14}*

According to Severinsen et al., the mean ± standard deviation 10MWT speed among stroke victims at the chronic stage is 0.84 ± 0.3 m.s^−1^ [65]. With an alpha coefficient of 0.05 (in two-tailed tests), a power of 80%, and a gait speed standard deviation of 0.3 m.s^−1^, we have calculated that a sample size of 280 patients (140 per group) will be needed to evidence a gait speed increment of 0.1 m.s^−1^ (a magnitude known to be clinically relevant after stroke [66–69]).

### Recruitment {15}

With an expected loss to follow-up rate of 10%, 300 patients (150 per group) will be included. To optimize inclusions, each center will screen inpatients upon admission to the stroke rehabilitation unit. Enrollment will continue until the recruitment target is reached (25 patients/site). We acknowledge that because of the COVID-19 pandemic, continuous inclusion will not be possible; hence, the enrollment period will extend over 6 years.

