**Methods:**

This multicenter (*n*=12), two-arm, parallel-group, randomized (1:1), controlled clinical study is a superiority trial. With *p*<0.05, a power of 80%, and an expected loss to follow-up rate of 10%, the inclusion of 300 patients will be required to evidence a 0.1-m.s^−1^ gain in gait speed. Trial will include adult patients (18–90 years) in the subacute phase (0 to 6 months after a hemispheric stroke) and who are able to walk for 10 m (with or without a technical aid). Registered physiotherapists will deliver a standardized GR program (30 min three times a week, for 4 weeks). The GR program will comprise various DTs (phasic, executive function, praxis, memory, and spatial cognition tasks during gait) in the DT (experimental) group and gait exercises only in the ST (control) group. The primary outcome measure is gait speed 6 months after inclusion. The secondary outcomes are post-stroke impairments (National Institutes of Health Stroke Scale and the motor part of the Fugl-Meyer Assessment of the lower extremity), gait speed (10-m walking test), mobility and dynamic balance (timed up-and-go test), ST and DT cognitive function (the French adaptation of the harmonization standards neuropsychological battery, and eight cognitive-motor DTs), personal autonomy (functional independence measure), restrictions in participation (structured interview and the modified Rankin score), and health-related quality of life (on a visual analog scale). These variables will be assessed immediately after the end of the protocol (probing the short-term effect), 1 month thereafter (the medium-term effect), and 5 months thereafter (the long-term effect).

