### Methods in analysis to handle protocol non-adherence and any statistical methods to handle missing data {20c}

This multicenter, randomized, controlled superiority trial will compare DT versus ST GR for all allocated patients with available data, on an intention-to-treat basis. A generalized linear mixed model could be used to compare the two groups with regard to the 10MWT speed or secondary outcomes.

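### Including 300 patients and losing 10% leaves 270, not the 280 that the sample size calculation requires; power on the plan's own inputs is about 78%, not 80%.

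*Protocol article*

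**What the plan says.** The Sample size {14} section takes a two-sided alpha of 0.05, 80% power, "a gait speed standard deviation of 0.3 m.s^−1" and a difference of 0.1 m/s. It concludes that "a sample size of 280 patients (140 per group) will be needed". It does not mention loss to follow-up.

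The allowance for loss comes in the next section, Recruitment {15}: "With an expected loss to follow-up rate of 10%, 300 patients (150 per group) will be included". That section also sets a target of 25 patients per site, which over 12 sites is again 300.

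The Methods part of the abstract joins the figures in one sentence: "a power of 80%, and an expected loss to follow-up rate of 10%, the inclusion of 300 patients will be required".

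On missing data, section {20c} says that the groups will be compared "for all allocated patients with available data, on an intention-to-treat basis". It adds that a generalized linear mixed model could be used. Section {20a} lists that model as one of several options for the primary outcome, after adjustment for age, center and NIHSS score.

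**The concern.** The 280 is the number needed for analysis, and the 300 is meant to be that number enlarged for a 10% loss. It is not enlarged enough. Taking 10% off 300 gives 270, which is below the stated requirement, and neither usual way of adding an allowance for loss turns 280 into 300.

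Sample size, loss and power for the single primary outcome are headline properties of the design. As written, the abstract attributes to the trial a power that it does not have on its own inputs. Readers will use the stated 80% to interpret a null or borderline result, so it should be a figure that the design supports.

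**Working it through.** **Inputs, all from the protocol article**

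- Difference δ = 0.1 m/s, SD σ = 0.3 m/s, two-sided alpha 0.05, power 80%: Sample size {14}
- Allocation 1:1: Trial design {8} and Sequence generation {16a}
- Number required: 280 (140 per group): Sample size {14}
- Loss 10%, inclusions 300 (150 per group): Recruitment {15}
- Analysis of allocated patients with available data: {18b} and {20c}

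**Step 1. Reproduce the 280.** For two means, n per group = 2(z₀.₉₇₅ + z₀.₈₀)²(σ/δ)² = 2 × (1.960 + 0.8416)² × (0.3/0.1)² = 141.3, so 142 per group (284 in total). The exact t-test calculation gives 143 per group (286). The stated 140 is within about 2% of both, so the base figure reproduces apart from rounding in the unfavourable direction. Power at exactly 140 per group is 79.6% (normal) or 79.4% (t).

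**Step 2. Apply the stated loss to the stated inclusions.** 300 × (1 − 0.10) = 270, or 135 per group. That is 280 − 270 = 10 patients short.

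**Step 3. Look for a rule that leads from 280 to 300.**

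- Dividing by the retained fraction: 280/0.90 = 311.1, so 312 (156 per group).
- Adding 10%, a common shortcut: 280 × 1.10 = 308.
- Loss that 300 can absorb: 1 − 280/300 = 6.7%.

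Neither rule gives 300. Starting from 284 or 286 instead of 280, division by 0.90 gives 316 or 318.

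**Step 4. Power at 135 per group, unadjusted.** The standard error of the difference is 0.3 × √(2/135) = 0.0365 m/s, so δ/SE = 0.1/0.0365 = 2.739.

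| Evaluable per group | Total | Power, normal | Power, t-test |
|---|---|---|---|
| 135 | 270 | 78.2% | 77.9% |
| 140 | 280 | 79.6% | 79.4% |
| 142 | 284 | 80.2% | 79.9% |
| 143 | 286 | 80.5% | 80.2% |

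The difference detectable with 80% power by the t-test is 0.103 m/s at 135 per group, against 0.101 m/s at 140.

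**Step 5. What adjustment would have to contribute.** Covariates explaining a share R² of the outcome variance reduce the residual SD to σ√(1 − R²). With 135 per group, 80% power by the t-test needs a residual SD of about 0.292 m/s, so R² = 1 − (0.292/0.3)² ≈ 0.05. If that came from baseline gait speed alone, the correlation with the 6-month speed would need to be about √0.051 = 0.23. The article gives neither quantity, so these are thresholds and not estimates.

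**The case against.** The strongest reply is that the effect is trivial. The loss allowance costs about 1.5 points (79.4% to 77.9%), the detectable difference moves by some 0.002 m/s, and the suggested remedy changes no patient, visit or analysis. This stands as a comment on importance. It does not make the stated figures consistent.

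A second reply is that the primary comparison is adjusted for age, center and NIHSS score, and about 5% of variance explained would restore 80%. That is plausible. But the calculation takes no credit for adjustment and the article gives no variance explained, so the claimed 80% does not rest on it.

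Third, patients lost before 6 months need not drop out entirely. Gait speed is measured at M0, M1, M2 and M6, and a repeated-measures mixed model would use the earlier visits. This softens the point, but section {20c} says only that such a model could be used, and the t-test and Mann-Whitney options use only patients with a 6-month value.

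Fourth, the gap between 140 and 142 or 143 per group is ordinary rounding. I agree, and the conclusion does not depend on it. Nor does it depend on the Mann-Whitney option. Power at 135 per group would be about 76% for normal data (relative efficiency 0.955), but that test would presumably be chosen when normality fails, and the 0.955 then no longer applies.

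Finally, the Trial status section hopes for more centers and participants. It sets no new target, so 300 remains the planned number.

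**Conclusion.** The concern holds. On the article's own inputs, 300 inclusions with 10% loss give 270 evaluable patients instead of 280, and 77.9% power (t-test) or 78.2% (normal approximation) instead of 80%. The 300 is consistent with a loss of up to 6.7%. The error lies in the allowance for loss and not in the 280, which reproduces to within rounding.

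These power figures assume an unadjusted comparison of two means at 6 months, SD 0.3 m/s, equal loss in both groups and no information recovered from patients without a 6-month value. Covariate adjustment or a repeated-measures model could close the gap, but the article neither fixes the model nor quantifies the gain. The practical consequence is small; what is wrong is a headline statement, repeated in the abstract.

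**What to change.** Keep 300 and correct the statement in Recruitment {15}, with Sample size {14} and the abstract aligned to it. Suggested text: *With 10% loss to follow-up, 300 inclusions leave 270 patients (135 per group), which gives about 78% power to detect 0.1 m/s at an SD of 0.3 m/s (two-sided alpha 0.05). The 280 evaluable patients are retained only if loss is at most 6.7%.*

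If the primary analysis is to rely on covariate adjustment, including any adjustment for baseline gait speed (not among the covariates now listed in {20a}), name the model, state the assumed correlation or variance explained with its source, and give the power under that model.

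The cost is a slightly less favourable power figure and no extra patients. Keeping both the 280 and the 10% loss would instead mean a target of 312 (156 per group), which is 12 more inclusions.

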## Assignment of interventions: allocation

### Sequence generation {16a}

The randomization procedure will be prepared by a data manager in the Clinical Research and Innovation Directorate (*Direction de la Recherche Clinique et de l'Innovation*, DRCI) at Amiens Picardie University Medical Center and implemented using Ennov Clinical® electronic data capture software (version 8.0.140, Ennov, Paris, France). The participants will be randomized (1:1) after inclusion and the baseline screening assessments at M0. To obtain groups that are balanced with regard to the stroke prognosis, stroke severity, and center, participants will be stratified by age (<45, 45 to 64, and ≥65), severity (according to the NIHSS score: < 5, 6 to 24, and ≥25), and center (1 to 12).

